| Réservé CRPV Reims : Cas RE.....                                                                                                                                                                                                                                                                                                                                                                                                                                                                                                                                                                                                                                                                                                                                                                                                                                                                                                                                                                                                                                                                                                                                                                                                                                                                                                                                                                                                                                                                                                                                                                                                                                                                                                                                                                               |                                                                                                                                                                                                                |                       |                       |                       |                                |                                |                                |                                |                              |             |                              |            |   |  |  |  |  |   |  |  |  |  |  |   |  |   |  |  |  |  |  |  |  |  |   |  |  |  |  |  |  |  |  |  |  |
| Chaque EIG doit être décrit sur une fiche séparée et numérotée Fiche ... sur ... pour le patient n° ..... 2/3                                                                                                                                                                                                                                                                                                                                                                                                                                                                                                                                                                                                                                                                                                                                                                                                                                                                                                                                                                                                                                                                                                                                                                                                                                                                                                                                                                                                                                                                                                                                                                                                                                                                             |                                                                                                                                                                                                                |                       |                       |                       |                                |                                |                                |                                |                              |             |                              |            |   |  |  |  |  |   |  |  |  |  |  |   |  |   |  |  |  |  |  |  |  |  |   |  |  |  |  |  |  |  |  |  |  |
| D- INFORMATIONS SUR LE(S) MEDICAMENT(S) ASSOCIES (à l'exclusion de ceux utilisés pour traiter l'événement)

  
 	DCI ou nom commercial	Voie d'administration	Dosage	Posologie	Date de début	Heure de début (si durée <24h)	Encore en cours	Date de fin	Heure de fin (si durée <24h)	Indication	
   
1											
 
2											
 
3											
  
                                                                                                                                                                                                                                                                                                                                                                                                                                                                                                                                                                                                                                                                                                                                                                                                                                                                                                            |                                                                                                                                                                                                                |                       | DCI ou nom commercial | Voie d'administration | Dosage                         | Posologie                      | Date de début                  | Heure de début (si durée <24h) | Encore en cours              | Date de fin | Heure de fin (si durée <24h) | Indication | 1 |  |  |  |  |   |  |  |  |  |  | 2 |  |   |  |  |  |  |  |  |  |  | 3 |  |  |  |  |  |  |  |  |  |  |
|                                                                                                                                                                                                                                                                                                                                                                                                                                                                                                                                                                                                                                                                                                                                                                                                                                                                                                                                                                                                                                                                                                                                                                                                                                                                                                                                                                                                                                                                                                                                                                                                                                                                                                                                                                                                                | DCI ou nom commercial                                                                                                                                                                                          | Voie d'administration | Dosage                | Posologie             | Date de début                  | Heure de début (si durée <24h) | Encore en cours                | Date de fin                    | Heure de fin (si durée <24h) | Indication  |                              |            |   |  |  |  |  |   |  |  |  |  |  |   |  |   |  |  |  |  |  |  |  |  |   |  |  |  |  |  |  |  |  |  |  |
| 1                                                                                                                                                                                                                                                                                                                                                                                                                                                                                                                                                                                                                                                                                                                                                                                                                                                                                                                                                                                                                                                                                                                                                                                                                                                                                                                                                                                                                                                                                                                                                                                                                                                                                                                                                                                                              |                                                                                                                                                                                                                |                       |                       |                       |                                |                                |                                |                                |                              |             |                              |            |   |  |  |  |  |   |  |  |  |  |  |   |  |   |  |  |  |  |  |  |  |  |   |  |  |  |  |  |  |  |  |  |  |
| 2                                                                                                                                                                                                                                                                                                                                                                                                                                                                                                                                                                                                                                                                                                                                                                                                                                                                                                                                                                                                                                                                                                                                                                                                                                                                                                                                                                                                                                                                                                                                                                                                                                                                                                                                                                                                              |                                                                                                                                                                                                                |                       |                       |                       |                                |                                |                                |                                |                              |             |                              |            |   |  |  |  |  |   |  |  |  |  |  |   |  |   |  |  |  |  |  |  |  |  |   |  |  |  |  |  |  |  |  |  |  |
| 3                                                                                                                                                                                                                                                                                                                                                                                                                                                                                                                                                                                                                                                                                                                                                                                                                                                                                                                                                                                                                                                                                                                                                                                                                                                                                                                                                                                                                                                                                                                                                                                                                                                                                                                                                                                                              |                                                                                                                                                                                                                |                       |                       |                       |                                |                                |                                |                                |                              |             |                              |            |   |  |  |  |  |   |  |  |  |  |  |   |  |   |  |  |  |  |  |  |  |  |   |  |  |  |  |  |  |  |  |  |  |
| E- EVENEMENT INDESIRABLE GRAVE
Désignation : .....

 
  Evénement grave car :
  Fatal
  Susceptible de mettre la vie en danger
  Provoque une hospitalisation* / prolongation d'hospitalisation existante
           Date d'admission : ..... Date de sortie : .....
 <small>*Exceptées les hospitalisations dont la durée et le but sont planifiés dans le protocole</small>
  Incapacité / invalidité persistante ou importante
  Grossesse / Anomalie congénitale à la naissance
  Intervention nécessaire pour éviter l'une des évolutions ci-dessus         
 
  Autre événement clinique / Laboratoire potentiellement grave (médicalement significatif comme décrit dans le protocole)         
 
 Période de survenue de l'EIG :
 Pendant la phase de sélection
 Pendant la phase d'administration du produit à l'essai
 Après l'arrêt de l'administration du traitement à l'essai (phase de suivi)
Date de début de l'EIG : /_/_/ /_/_/ /_/_/ /_/_/ et heure de survenue (si EIG <24h) : .....
Description (Diagnostic : décrire la chronologie de l'événement. Joindre les compte-rendus anonymisés d'hospitalisation, d'examen et/ou résultats de laboratoire si nécessaire)
_____
_____
Mesures thérapeutiques prises :  Non  Oui, si oui description : _____ |                                                                                                                                                                                                                |                       |                       |                       |                                |                                |                                |                                |                              |             |                              |            |   |  |  |  |  |   |  |  |  |  |  |   |  |   |  |  |  |  |  |  |  |  |   |  |  |  |  |  |  |  |  |  |  |

CRPV de Reims – [name] - Hôpital Robert Debré - [name]

Fiche ... sur ...

pour le patient n° .....

3/3

## E- EVENEMENT INDESIRABLE GRAVE

Disparition de l'EIG après arrêt du ou des traitement(s) à l'essai : ☐ Oui (n° 1 - 2 - 3)\* ☐ Non ☐ Sans objet

Réapparition de l'événement après réintroduction du ou des traitement(s) à l'essai : ☐ Oui (n° 1 - 2 - 3)\* ☐ Non ☐ Sans objet

Evolution de l'événement :

☐ Guérison sans séquelle

☐ Guérison sans séquelle

☐ Sujet non encore rétabli avec évolution par rapport à l'état initial : ☐ Améliorée ☐ Inchangée ☐ Aggravée

☐ Décès : ☐ En rapport avec l'EIG ☐ Sans rapport avec l'EIG

Date du décès / / / / / / / / / /

Autopsie : ☐ Oui (joindre le rapport d'autopsie si disponible) ☐ Non

## F- MESURES PRISES SUITE A L'EIG

Produit(s) à l'essai

☐ Traitement poursuivi sans changement

☐ Modification de dose(s) : Nouvelle posologie : ..... depuis le .....

☐ Arrêt temporaire du traitement à l'essai (n° 1 - 2 - 3)\* du ..... au .....

☐ Arrêt définitif du traitement à l'essai (n° 1 - 2 - 3)\* : Date de fin : .....

☐ Non applicable

L'EIG a conduit à un arrêt des médicaments associés : ☐ Non ☐ Oui, si oui numéro 1 - 2 - 3 : ☐ Arrêt temporaire

- ☐ Arrêt temporaire
- ☐ Arrêt définitif

## G- EVALUATION DU LIEN DE CAUSALITE

Selon l'investigateur l'ELG semble plutôt lié :

☐ au(x) traitement(s) à l'essai (n°1 - 2 - 3)\*

☐ autre cause : ☐ traitement associé (n°1 - 2 - 3)\*

☐ maladie intercurrente

- ☐ progression de la maladie

☐ autre raison : .....

☐ information insuffisante

CADRE RESERVE AU CRPV

Selon le promoteur l'EIG semble plutôt lié :

☐ au(x) traitement(s) à l'essai (n°1 - 2 - 3)\*☐ autre cause :      ☐ traitement associé (n°1 - 2 - 3)\*☐ maladie intercurrente☐ progression de la maladie

☐ autre raison : .....

suffisante

Si l'ELG est lié au médicament

☐ l'événement indésirable est att

☐ l'événement indésirable est inattendu

\*Entourer le numéro de traitement correspondant

Nom de l'investigateur : ..... Date : ..... Signature : .....

CRPV de Reims – [name] - Hôpital Robert Debré - [name]

#### 8.4. Methods and duration of follow-up of subjects following the development of an adverse event

See section 8.2.

## 9. STATISTICS

### 9.1. Description of the statistical methods planned, including the timetable for any intermediate analyses if applicable

#### Global analysis

The analysis of the primary evaluation criterion will be carried out by a detailed breakdown as soon as the development of an adverse event(s) necessitates the termination of eplerenone treatment (see section 4.2). This will be a descriptive analysis.

The analysis of the secondary criteria will be descriptive and comparative between before and under eplerenone treatment.

Discontinuous variables will be expressed as percentages and continuous variables as the mean  $\pm$  standard deviation.

#### Intermediate analyses

Not applicable.

### 9.2. Number of subjects to include in the study with statistical justification and theoretical number of patients expected in each place of study, if applicable

The anticipated number of subjects to include in the study is 31 patients.

See section 5.3 for the procedure for termination of the study

See section 9.3 for the justification of number of patients to include

See section 9.1 for the methods of analysis of the data

### 9.3. Size of the sample / population

#### 9.3.1 Calculation and/or justification of the number of subjects required

##### 9.3.1.1. Baseline hypothese(s) for this calculation:

According to data in the literature, the probabilities of hyperkalaemia developing during 8 weeks of eplerenone treatment are <7% with the 25 mg dose and <10% with the 50 mg dose (Gonzalez Monte *et al.*, 2010, Pitt *et al.*, 2003, Pitt *et al.*, 1999, Zannad *et al.*). We posed the alternative hypothesis that it is not useful to continue the study if the risk of hyperkalaemia is >15% with the 25 mg dose and 20% with the 50 mg dose.

The power for detecting an adverse event requiring the termination of treatment was fixed at 90%.

Under these hypotheses, it is possible to carry out a study in several steps by adapting the 2-step scheme proposed by Simon (Simon, 1989) in the following way:

First step: 14 patients will be included at the dose of 25 mg and followed for 8 weeks: if  $\geq 4$  patients experience an adverse event requiring the termination of treatment, the study will be stopped. In the opposite case, 17 additional patients will be included at the same dose for 8 weeks. If  $\geq 5$  patients out of the 31 have a limiting toxicity, the alternative hypothesis can be rejected and the study will be stopped; in the opposite case, the dose will be increased to 50 mg for 31 patients with a follow-up at 6 months. If at the end of this follow-up,  $\leq 4$  patients have a limiting toxicity with the 50 mg dose, the alternative hypothesis will be rejected and continuation of the study with eplerenone will be possible.

In these conditions, the probability of demonstrating a limiting toxicity greater than the fixed norms is 90.0%, the risk of stopping the study wrongly is 27.6%.

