**Plan for the statistical analysis**

According to data in the literature, the probabilities of hyperkalaemia occurring during 8 weeks of treatment with eplerenone are <7% with a dose of 25 mg and <10% with a dose of 50 mg in non-transplanted patients with an eGFR >50 mL/min. We posed the alternative hypothesis that the study should be stopped if the risk of poor tolerance of treatment is >15% with the 25 mg dose and 20% with the 50 mg dose. The power to detect an adverse event requiring the termination of treatment was fixed at 90%. The number of subjects necessary to include is 31 patients.

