### 4. STUDY CONCEPTION

#### 4.1. Evaluation criteria

##### **Primary criterion: *appearance of adverse events requiring the termination of treatment***

The adverse events requiring the termination of treatment that will be considered are:

- hyperkalaemia  $\geq 6$  mmol/L and/or hyperkalaemia  $\geq 5.5$  mmol/L under 2 spoon-measures/day of KAYEXALATE®
- acidosis revealed by an alkaline reserve  $\leq 15$  mmol/L
- systemic arterial hypotension revealed by a systolic arterial pressure  $< 100$  mmHg
- orthostatic hypotension defined by a decrease in systolic arterial pressure of  $> 20$  mmHg in the 3 minutes following standing
- acute renal failure defined by an increase in creatininaemia of  $> 30\%$  compared to its value at inclusion
- all other unexpected adverse events requiring the termination of eplerenone treatment

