**4.2. Description of the study methodology****Study scheme (Figure 1)**

The tolerance study will be carried out by adapting the 2-step scheme of Simon (Simon, 1989) initially, and then by carrying out an increase in doses if tolerance is satisfactory.

From the data in the literature, it appears that the frequency of intolerance to treatment is <7% for a dose of 25 mg/day and <10% for a dose of 50 mg/day, which seems acceptable in this population and leads us to envisage a subsequent therapeutic trial. Conversely, its use does not appear possible if the respective frequencies are >15% and 20%, respectively.

In these conditions, for this tolerance study, we proposed a scheme which includes three successive stages combining the plan of Simon in two stages at a dose of 25 mg/day, and then an increase in dose to 50 mg/day with evaluation at a single time (Figure 1).

Under these conditions, the risk of not revealing unacceptable tolerance of eplerenone in this population is <10% and the risk of deciding, if tolerance permits, to not use it is 27%. There is a 60% chance of interrupting the study before the increase in dose if the hypothesis of unfavourable treatment is correct.

The advantages of the study scheme are that it will demonstrate unacceptable toxicity as early as possible and will detect a possible threshold effect between the doses of 25 mg/day and 50 mg/day which will allow the use of the lowest dose possible.

**Step 1:** 14 patients will be included in the first step, at an eplerenone dose of 25 mg/day. This stage will last 8 weeks. If  $\geq 3$  adverse events requiring the termination of treatment occur during these 8 weeks, the study will be stopped and the treatment will be considered to be too poorly tolerated to be used in this population. If <3 adverse events occur, we will proceed to step 2.

**Step 2:** This will consist of the addition of an additional 17 patients. All of the patients (14+17) will be treated with eplerenone at a dose of 25 mg/day for 8 weeks. If >4 adverse events requiring the termination of treatment occur during the 8 weeks, the study will be stopped and the treatment will be considered to be too poorly tolerated to be used in this population. If  $\leq 4$  adverse events occur, we will proceed to step 3.

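### Section 9.3.1.1 sets the design rates for hyperkalaemia while the stopping rule counts a six-item composite, so the stated 27.6% wrong-stopping risk holds only if 7%/10% are composite rates

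*Protocol*

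**What the plan says.** Section 9.3.1.1, which justifies the 31 patients, gives the acceptable rates as "the probabilities of hyperkalaemia developing during 8 weeks of eplerenone treatment are <7% with the 25 mg dose and <10% with the 50 mg dose". Its alternative reads: "it is not useful to continue the study if the risk of hyperkalaemia is >15% with the 25 mg dose and 20% with the 50" (the last figure being the higher dose in mg). Both hypotheses are therefore about hyperkalaemia.

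The same four figures carry other labels elsewhere:

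- **Summary, Plan for the statistical analysis:** 7%/10% are hyperkalaemia probabilities "in non-transplanted patients with an eGFR >50 mL/min", but 15%/20% are something wider: "the study should be stopped if the risk of poor tolerance of treatment is >15% with the 25 mg dose and 20% with the 50" (again the higher dose in mg).
- **Section 4.2:** both pairs describe intolerance. It says "the frequency of intolerance to treatment is <7% for a dose of 25 mg/day and <10% for a dose of 50 mg/day", and then "its use does not appear possible if the respective frequencies are >15% and 20%, respectively".
- **Section 9.3.1.2:** 15%/20% are the anticipated maximum of adverse events that require eplerenone to be stopped.

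The event counted against the limits is defined in section 4.1 and repeated in 5.3.1. It has six items: hyperkalaemia at a stopping level, acidosis, low systolic pressure, an orthostatic fall, "acute renal failure defined by an increase in creatininaemia of" more than 30% over the inclusion value, and any other unexpected event that requires termination. No rate is given for the five items other than hyperkalaemia.

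Section 9.3.1.1 states a 90.0% chance of detecting excessive toxicity and a 27.6% risk of stopping wrongly.

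**The concern.** A hypothesis about hyperkalaemia and a count of six kinds of event are different quantities. Suppose hyperkalaemia sits exactly at the rate that 9.3.1.1 treats as acceptable. Any patient who stops for acidosis, blood pressure, creatinine or another cause then pushes the count towards the limit, and 27.6% makes no allowance for this.

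The count decides whether eplerenone is declared too poorly tolerated for this population. Under the wording of 9.3.1.1, a stop driven by pressure or creatinine events could be reported as hyperkalaemia above 15% or 20%, which the count would not show.

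**Working it through.** **Inputs.** Rates of 7%/10% and 15%/20% (sections 4.2, 9.3.1.1, Summary). Step 1: 14 patients, stop at 3 or more (section 4.2) or at 4 or more (section 9.3.1.1). Step 2: 14 + 17 = 31 patients, stop at a total of 5 or more. Step 3: 31 patients at 50 mg, stop at 5 or more. No loss to follow-up (section 9.3.1.5).

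**Formula.** Let p be the 25 mg rate and q the 50 mg rate of the counted event, with X1 ~ Bin(14, p), X2 ~ Bin(17, p) and X3 ~ Bin(31, q), all independent.

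P(stop) = 1 − P(X1 ≤ 2 and X1 + X2 ≤ 4) × P(X3 ≤ 4)

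**Reproducing the plan's figures (step-1 limit of 3).**

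- p = 0.07, q = 0.10: 1 − 0.8971 × 0.8068 = 0.276. The plan states 27.6%.
- p = 0.15, q = 0.20: 1 − 0.4359 × 0.2287 = 0.900. The plan states 90.0%.

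With the step-1 limit of 4 given in 9.3.1.1 itself, the results are 24.6% and 88.8%. The stated figures therefore belong to the section 4.2 limit, with 31 patients counted afresh in step 3. In either case p and q are rates of the *counted* event, with nothing added for the other components.

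**If 7%/10% is hyperkalaemia alone.** The documents give no rates for the other items. Assume that they add a risk a per step, independent of hyperkalaemia and equal at both doses. The composite rate is then 1 − (1 − h)(1 − a), where h is the hyperkalaemia rate. For a = 2%: 1 − 0.93 × 0.98 = 8.9% and 1 − 0.90 × 0.98 = 11.8%.

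| Added risk a (assumed) | Composite rate, 25/50 mg | P(stop), step-1 limit 3 | P(stop), step-1 limit 4 | Limit 3, step 3 in remaining patients only |
|---|---|---|---|---|
| 0 | 7.0% / 10.0% | 27.6% | 24.6% | 24.7% |
| 1% | 7.9% / 10.9% | 35.3% | 32.0% | 31.7% |
| 2% | 8.9% / 11.8% | 43.3% | 39.8% | 39.1% |
| 3% | 9.8% / 12.7% | 51.3% | 47.8% | 46.6% |
| 5% | 11.7% / 14.5% | 66.1% | 63.1% | 61.0% |

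Up to a = 3%, each added point raises the first P(stop) column by about 8 points.

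**If stopping-level hyperkalaemia is rarer than the benchmark** (rates again assumed, step-1 limit 3):

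- 5%/8% plus 2% other: composite 6.9%/9.8%, P(stop) 26.5%.
- 4%/7% plus 3% other: composite 6.9%/9.8%, P(stop) 26.2%.
- 4%/7% plus 2% other: composite 5.9%/8.9%, P(stop) 19.1%.
- A composite of 6%/9%, however made up: P(stop) 19.9%.

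**Power.** P(stop) rises with p and q, so components added on top of 15%/20% can only raise the 90.0%.

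**The case against.** A reader might infer that 27.6% is simply too low. The documents do not show that. Section 4.2 gives 7%/10% as a frequency of intolerance, and on that reading 27.6% is exactly right. The rates are also upper bounds. The benchmark is hyperkalaemia with no potassium threshold stated, whereas the counted item is narrower: at least 6 mmol/L, or at least 5.5 mmol/L under two daily measures of resin, and section 8.2 puts diet and resin steps before it. The added components may therefore be offset, in part or in full. This objection stands, and the upward figures must remain conditional.

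A reader might also infer that all four limits are hyperkalaemia rates throughout. For 15%/20% that is so only in 9.3.1.1; the Summary, 4.2 and 9.3.1.2 tie them to poor tolerance, intolerance or treatment-stopping events.

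The difference in population adds little. The Summary discloses it, section 2.6 explains why this population was chosen, and section 4.2 uses 7%/10% as a level acceptable in this population, not only as a forecast.

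Calling a stop at a composite of 11.7%/14.5% wrong judges it on hyperkalaemia alone, while the primary objective in 3.1 is tolerance as a whole. Section 9.1 also plans a detailed breakdown of the primary criterion, so the cause of a stop should be visible. Any error from extra components is on the cautious side.

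None of this removes the conflict in the text: 9.3.1.1 words its hypotheses for one quantity and applies them to another.

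**Conclusion.** The point holds as an inconsistency that needs correcting, with a conditional effect on the stated risk. It is certain that the same figures are labelled differently in the Summary, 4.2, 9.3.1.1 and 9.3.1.2, that the rule counts the composite, and that 27.6% and 90.0% are reproduced only with 7%/10% and 15%/20% as composite rates.

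The size is conditional. With hyperkalaemia alone at 7%/10% and an assumed independent 1% to 5% from other causes, wrong stopping would be about 35% to 66%. With stopping-level hyperkalaemia below the benchmark it could be at or below 27.6%; the assumed examples give 19% to 27%. The protocol does not fix which case applies, so a flat statement that the risk is understated goes too far. The chance of stopping for unacceptable toxicity is not reduced by added components.

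**What to change.** 1. Word both hypotheses in the Summary and in 9.3.1.1 for the composite listed in section 4.1, in line with 4.2 and 9.3.1.2.
2. Say in 9.3.1.1 that 27.6% is conditional on composite rates of 7%/10%, and give the wrong-stopping risk over a short range of composite rates on both sides, for example 19.9% at 6%/9%, 27.6% at 7%/10%, 35.3% at 7.9%/10.9% and 51.3% at 9.8%/12.7%. These values use the step-1 limit of 3.
3. Within the breakdown planned in 9.1, present the hyperkalaemia component separately, so that a stop is not read as hyperkalaemia above 15% or 20%.
4. Reconcile the step-1 limits (3 or more in 4.2, 4 or more in 9.3.1.1) and restate the risks for the limit that is kept. The current figures match only the limit of 3; which limit applies is for the investigators to decide.

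The cost is some wording and a small table. No extra patients or data are needed. The downside is that a single stated risk becomes a conditional range, part of which is less favourable.
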